### Inclusion of participants

Potential participants will be identified and recruited by the staff in the paediatric wards. Inclusion criteria are as follows: age 0–24 months, hospitalised on the basis of acute airway infection, born in gestational week 35 or later. Patients must be included within 24 h of hospital admission. At least one of the parents/guardians needs to understand written Swedish, English, Arabic, or Persian. Exclusion criteria are as follows: previous respiratory or cardiac diagnoses.

To include adequate participants, the study will be mentioned at two pulse meetings a day in the wards, and all staff members will be trained in the study design. Some staff members will get additional training to support their colleagues. The main investigator will regularly visit the wards in person and will have telephone communication in between the visits to remind the staff and to answer questions.

First, the parents will receive written information about the study (text in Swedish, Arabic, English, or Persian). At that time and when they have had the opportunity to read the information, they may ask questions and get additional information from the staff. In order to admit their child into the study, the parent/s will sign a written consent form. The participation in the study will end when the infant is either discharged to the home or referred to an intensive care unit or if the parents decide to withdraw the participation of their child.

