#### Secondary outcome measures

The clinical status of the participants will be assessed by the nursing staff and the parents using the measures in Table 2. Wang score [31] is an observational scale where the nursing staff scores the infants 0–3 where 3 is most severe. The scoring system includes respiratory rate, wheezing, retractions/nasal flaring, and general condition. It has been validated in clinical studies [31–33]. The respiratory rate, retractions, and wheezing is commonly used in studies of bronchiolitis, and the inter-observer agreement is good: 93.1% with a weighted kappa of 0.72 (95% CI 0.66–0.78) [33].

**Table 2 Tab2:** The secondary outcome measures, reported by the clinical staff unless otherwise stated

Secondary outcome	Measure	Registration time
Wang respiratory score [31]		
Respiratory rate	Manual count, per minute. Scale 0–3 where 3 is worst	At baseline, 20 min later and every 3rd hour
Wheezing sound	Clinical observation. Scale 0–3 where 3 is worst	At baseline, 20 min later and every 3rd hour
Retractions/nasal flaring	Clinical observation. Scale 0–3 where 3 is worst	At baseline, 20 min later and every 3rd hour
General condition	Clinical observation. Scale 0–3 where 3 is worst	At baseline, 20 min later and every 3rd hour
General condition (parents’ report)	Observation. Scale 0–10 where 10 is worst	At baseline, 20 min later and every 3rd hour during daytime
Food intake (parents’ report)	Observation. Scale 0–2 where 2 is worst	At baseline, 20 min later and every 3rd hour during daytime
Body weight	Naked weight on scales, g	Once daily
Heart rate	Counts per minute, by pulse-oximetry, probe on the foot	At baseline, 20 min later and every 3rd hour
Time to recovery	Time at hospital, hours	At the end of the study
Lung complications	Referral to intensive care unit—yes/no	At the end of the study

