#### Statistical and sample size calculations

Descriptive statistics will be shown as mean with standard deviation or median with minimum and maximum values for continuous and ordinal variables where appropriate. Number with percent will be shown for categorical variables.

The primary outcome is clinical index at 24 h. The time is chosen since our experience is that most infants will remain at hospital at that time and an effect should have been shown. The effect of the individualised physiotherapy intervention, the non-individualised intervention, and a control group receiving standard care on clinical index at 24 h will be assessed by an ANCOVA model with adjustment for baseline clinical index, and post hoc test for the different group combinations will be performed.

The secondary outcomes, including clinical index at 20 min, will first be assessed by an overall test and if the overall test is shown significant post-hoc tests will be performed. A *p* value below 0.05 will be considered significant for the overall test. Continuous and ordinal variables will be assessed by ANCOVA model with adjustment for baseline values where possible, ANOVA, or Kruskal-Wallis test, with *t* test or Mann-Whitney *U* test as post hoc tests, where appropriate. Categorical variables will be assessed by Fisher’s exact test. Explorative subgroup analyses by gender will be performed. To increase the knowledge about what time the infants will recover, data are collected every 3 h. We will analyse the time the infants recover by means of Fisher’ exact test and Kaplan-Meier analysis. IBM SPSS Statistics 24, or higher, Windows (IBM Corporation, Armonk, NY, USA) will be used to perform the statistical analyses.

The primary analysis will include all participants with available outcome data at 24 h. Drop-outs will not be included in this analysis. A dataset with the imputed values might also be analysed. Simple imputation, mean of the value before and after the missing value or last value carried forward from the assessment three hours earlier, will be performed if data is missing at hour 24 and the patient is still at hospital. If an infant will be discharged from the ward before hour 24, that participant will be excluded from this analysis and will be analysed in the same way as the other potential drop-outs.

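### Time to recovery is given Fisher's exact test with no cut hour and Kaplan-Meier with no comparison test, and neither is named as the overall test at 0.05

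*Protocol article*

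**What the plan says.** All the analysis statements are in the protocol article under Statistical and sample size calculations.

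- Secondary outcomes "will first be assessed by an overall test and if the overall test is shown significant post-hoc tests will be performed". The stated level is a p "value below 0.05 will be considered significant for the overall test".
- By type of variable: "Continuous and ordinal variables will be assessed by ANCOVA model with adjustment for baseline values where possible, ANOVA, or Kruskal-Wallis test", and "Categorical variables will be assessed by Fisher’s exact test".
- On recovery: "To increase the knowledge about what time the infants will recover, data are collected every 3 h". The next sentence reads: "We will analyse the time the infants recover by means of Fisher’ exact test and Kaplan-Meier analysis".

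Table 2, under Secondary outcome measures, lists time to recovery, measured as "Time at hospital, hours" and registered at the end of the study.

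Under Inclusion of participants: "The participation in the study will end when the infant is either discharged to the home or referred to an intensive care unit". Withdrawal by the parents also ends it.

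**The concern.** The sentence on recovery time is a positive statement of method, and it leaves three things open.

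1. A duration cannot enter Fisher's test until it is turned into recovered or not recovered by a given hour. The hour is not stated, and a 3-hourly grid offers many.
2. Kaplan-Meier gives curves and medians. It gives a p value only when paired with a comparison such as the log-rank test, which the article does not name.
3. The same section sends each secondary outcome through a single overall test that opens the way to post hoc comparisons. For recovery time the reader cannot tell which result is that test.

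The Discussion motivates the trial partly by the need to reduce hospitalisation, so a claim of faster recovery would be prominent. With two unranked methods and a free cut hour, such a claim could rest on whichever result crosses 0.05. A single cut also gives up timing information that the 3-hourly data were collected to provide.

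**Working it through.** **The plan's own figures.** The article gives no error rate or power for recovery time. Its sample size supplies the arm sizes and reproduces. With difference 2, SD 2.8, two-sided alpha 0.016 and power 0.80, the exact t calculation gives 43 per group (power 0.801). Then 43/0.80 = 53.75, rounded up to 54, and 3 × 54 = 162.

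**Assumed inputs (not in the documents).** Log-normal stay with median 60 h; log-SD 0.5, 0.6 or 0.8; times rounded up to the 3 h grid; no censoring; candidate Fisher hours 24, 48 and 72. Arms of 43 or 54.

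**Tests.** Three-arm log-rank (chi-square, 2 df) and the exact Fisher test on the 3 × 2 table of recovered by hour c or not, each at 0.05.

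**Upper guide.** If k tests were independent, the chance of at least one false positive is 1 − 0.95^k:
- k = 2: 1 − 0.9025 = 9.8%
- k = 4: 1 − 0.8145 = 18.5%

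Tests on the same infants are correlated, so the true figures should be lower.

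**Simulation under no effect** (3,000 trials per row):

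| Per arm | Log-SD | Log-rank alone | Fisher 48 h alone | Log-rank or Fisher 48 h | Log-rank or Fisher 24, 48 or 72 h |
|---|---|---|---|---|---|
| 43 | 0.5 | 5.0% | 4.0% | 8.2% | 12.1% |
| 43 | 0.8 | 5.5% | 3.7% | 8.1% | 14.0% |
| 54 | 0.5 | 5.0% | 4.4% | 8.6% | 13.0% |
| 54 | 0.8 | 5.1% | 5.0% | 8.8% | 14.0% |

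The Monte Carlo standard error near 9% is √(0.09 × 0.91/3000) = 0.5 percentage points.

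A separate simulation at log-SD 0.6 gave 8-10% for log-rank or Fisher at 48 h, and 13-15% for log-rank or Fisher at any of the three hours. Fisher alone, at whichever of the three hours is significant, gave 11-12%. Any one designated test stayed between 1.9% and 5.5% in the tabulated runs.

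**Simulation with an assumed effect** (medians 60, 52 and 45 h, log-SD 0.6):

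| Run | Log-rank power | Fisher 48 h power | The two disagree |
|---|---|---|---|
| First, 43 per arm | 42% | 30% | 28% |
| First, 54 per arm | 50% | 37% | 30% |
| Second, 43 to 54 per arm | 44-52% | 32-41% | 28-29% |

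Fisher at one hour is therefore about 11 to 14 points less powerful in these settings, and the two tests give opposite verdicts in more than a quarter of trials.

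**The case against.** **The specific sentence may replace the general rule.** A reader might infer that recovery time gets Fisher and Kaplan-Meier in addition to ANOVA or Kruskal-Wallis. The text does not establish that. A specific sentence following a general rule can be read as overriding it. The sentence may also concern recovery status on the 3 h grid, which is a different variable from the single hospital time in Table 2. This objection stands, so the point does not rest on a third test; the figures above leave Kruskal-Wallis out.

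**Kaplan-Meier may be descriptive only.** Then Fisher supplies the only p value. This is a fair reading, but it does not remove the problem: the open hour alone gives 11-12% with three candidate hours.

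**Much larger inflation.** A reader might infer a figure near 38%. That arises if Kruskal-Wallis, log-rank and Fisher at every 3 h cut from 24 to 144 h may all count, and (144 − 24)/3 + 1 = 41 cuts. The article proposes no such search and does not say the hour will be picked from the results, so the figure should not be used.

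**Detail left to an analysis plan.** A Fisher hour, or the test that accompanies the curves, is often fixed there, and such a plan may exist. This limits what can be said about intent. It does not cover an article that itself names two unranked methods for one outcome beside a rule requiring one overall test.

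**Fisher at a fixed hour is valid.** This is true. The case against it is lower power and the missing hour, not invalidity.

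**Conclusion.** The point holds as a moderate correction to one secondary outcome. The article names two methods for recovery time, fixes no hour for Fisher, names no comparison for the Kaplan-Meier curves and does not say which is the overall test. Whether the ANOVA or Kruskal-Wallis rule also applies is unclear.

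If either log-rank or Fisher at one hour may count, the false-positive chance is about 8-10%; with three Fisher hours it is about 12-15%, against a nominal 5%. Fisher at 48 h has roughly 32-41% power where log-rank has 44-52%.

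These sizes depend on the assumed stay distribution, the assumed hours and medians, and the absence of censoring. They also assume that a log-rank test would accompany the curves, which the article does not say. A reader might infer that the trial's main conclusion is at risk. It is not: the 24 h clinical index, its alpha and the total of 162 are untouched.

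**What to change.** Revise the recovery-time sentence under Statistical and sample size calculations so that it:

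1. names one three-arm log-rank test as the overall test for time to recovery, with pairwise log-rank tests only if it is significant;
2. states that this replaces the ANOVA or Kruskal-Wallis rule for this outcome, and whether the time analysed is Table 2's time at hospital;
3. states that ICU referral is not counted as recovery at the moment of referral, and how referral and withdrawal enter the analysis, since both end participation without recovery;
4. makes Kaplan-Meier curves, medians and any proportion recovered by a given hour descriptive;
5. keeps Fisher's exact test for ICU referral (yes/no).

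Stratifying the log-rank test by site would match the randomisation but is optional.

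The cost is a wording change with no new data and no change in sample size. The downside is that the proportion recovered at a fixed hour loses its own significance test.

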**Methods:**

This study is a clinical two-centre individually randomised controlled trial (RCT) with three parallel groups. The participants will be randomly assigned to an individualised physiotherapy intervention, a non-individualised intervention, or a control group. All three groups will receive the standard care at the ward, and the two intervention groups will receive additional treatment, including different movements of the body. The primary outcome measure is a clinical index based on determinants for hospitalisation. Baseline assessments will be compared with the assessments after 24 h. The secondary outcome measures include vital signs, the parents’ observations, time spent at the hospital ward, and referrals to an intensive care unit. We also want see if there is any immediate effect of the first intervention, after 20 min.

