## Background

Infants with acute breathing difficulties due to a lower respiratory tract infection such as bronchiolitis or pneumonia often have obstruction of the smaller airways caused by oedema and excess mucus production [1]. This can lead to increased work of breathing with exhaustion of respiratory muscles, feeding difficulties, and increases the risk of developing respiratory distress. Affected infants may need treatment at an intensive care unit (ICU). The hospital care for the children with bronchiolitis involves a high cost for families and health care organisations around the world [2], as this is a common illness in the winter season [3]. The treatment in hospitals is most often supportive, such as supplementing oxygen and fluids [4].

Sometimes, physiotherapy treatment is used to reduce the symptoms of infants who are hospitalised with bronchiolitis. Physiotherapy methods aim at moving and evacuating mucus from the airways in order to reduce work of breathing, increase gas exchange, and increase lung volumes [5–7]. The aim of physiotherapy treatment has also been to reduce time to clinical stability or reduce the duration of a hospital stay [8, 9]. There is no clear consensus about the efficiency of physiotherapy treatment on the whole for this patient group, and some of the treatment methods are questioned or not recommended at all [10, 11].

Many of the physiotherapeutic interventions that are described in international literature for infants hospitalised with breathing difficulties such as bronchiolitis or pneumonia can be described as passive: the physiotherapist places the child in different drainage or resting positions, applies manual pressure to the child’s chest wall, or uses technical devices like continuous positive airway pressure (CPAP) or positive expiratory pressure (PEP) [5, 8, 9, 12–21]. In Sweden, however, physiotherapy for infants in hospital with acute airway infections most often involves stimulation to physical activity and frequent changes of the body position combined with other methods [22]. This praxis is supported by general physiological principles of the positive effect on lung function of the change of body positions and physical activity [23–25], but these methods have not been evaluated scientifically for this patient group before, and that is why this study was designed.

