The infant’s food intake will be reported by the parents by a custom-made three-level scale 0–2 where 0 = no self-contained eating at all, 1 = eats less than usual, and 2 = eats as usual. The infant’s general condition will be reported by the parents using a visual numeric rating scale 0–10 where 0 = as usual and 10 = very affected/ill. The numeric rating scale 0–10 has been validated for assessing pain [34], for cancer-related symptoms such as pain and severe tiredness [35], and for postoperative nausea [36] and patient-specific function [37]. It has also been used to assess different symptoms in studies although not validated for this, like well-being, depression, fatigue, and anxiety [38].

Body weight will be used to calculate the daily food/fluid need, and heart rate might show cardiorespiratory load or stress.

Time at hospital and referrals to ICU as a measure of severity of the disease have also been used in other studies [5].

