The sample size is calculated on a two-sided two sample *t* test with equal variance. The mean difference that we want to be able to detect in clinical index at 24 h is 2. A previous pilot study (unpublished material) has shown that the standard deviation is approximately 2.8. The power probability for the test is 0.80, and to be able to correct for the three primary tests, comparing the individualised physiotherapy intervention, the non-individualised intervention, and a control group receiving standard care with each other, the type I error probability in the calculation is 0.016, confidence interval 0.95. To be able to detect the difference, 43 evaluable patients in each group is needed. The calculation is performed in SAS Enterprise Guide 6.1 for Windows (SAS Institute Inc., Cary, NC, USA). Incomplete observations and drop-outs are expected to amount to about 20%. Thus, a total of 162 patients are needed to be included in the study. The drop-outs will be analysed according to age, possible viral infection, gender, allocation group, and severity of illness at admission to the ward (saturation, respiratory rate and heart rate or more data if collected). We plan to perform an interim analysis of the data obtained after inclusion of 50% of the estimated sample size in order to check the assumptions about the standard deviation and recalculate the sample size. In that analysis, we will also be able to address possible safety concerns in the study, although we do not anticipate any harmful outcome. That analysis will be performed by a statistician independent of the study, and the result will only be presented to the research group at this stage if any harmful outcome will be detected in the intervention groups, such as significant inferior outcomes in the intervention groups compared to the control arm. Further instructions will be discussed by the trial team before the interim analysis.

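### Time to recovery is read from hospital or ward time by Kaplan-Meier, but participation ends at intensive care referral as well as at discharge home, so a deteriorating infant is not counted as unrecovered

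*Protocol article*

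**What the plan says.** All references are to the protocol article.

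- **Measure.** Table 2 (Secondary outcome measures) lists time to recovery, measured as "Time at hospital, hours" and registered at the end of the study. The Methods paragraph of the abstract calls it "time spent at the hospital ward". The text below Table 2 treats it as a severity measure: "Time at hospital and referrals to ICU as a measure of severity of the disease have also been used in other studies". A shorter time is therefore read as better.
- **End of follow-up.** Inclusion of participants: "The participation in the study will end when the infant is either discharged to the home or referred to an intensive care unit". Parental withdrawal is the third way out.
- **Analysis.** Statistical and sample size calculations: "We will analyse the time the infants recover by means of Fisher’ exact test and Kaplan-Meier analysis". The section does not say what counts as recovery or what is censored. Its only rule for infants who leave early concerns the 24 h analysis of the clinical index.
- **Referral.** Table 2 has it as a separate item, "Referral to intensive care unit—yes/no", with no link to time to recovery.

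**The concern.** The best outcome (going home) and a bad one (deterioration leading to intensive care) stop the same clock. Kaplan-Meier needs each infant's time labelled as event or censored. Under the stated end of participation, two labels are open for a referred infant:

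1. **Event.** The time to referral is taken as the length of stay, so a sick infant enters as an early recovery.
2. **Censored.** The infant is assumed to have the same prospect of going home as those still on the ward, although it left the ward because it was doing worse.

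Neither label counts the infant as unrecovered. If the arms differ in referral, the comparison of recovery times is distorted in favour of the arm with more referrals. The outcome is secondary, but it is the one that families and wards would read as how soon the child goes home.

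**Working it through.** **The plan's own figures.** There is none for time to recovery and no referral rate. The sample size belongs to the clinical index at 24 h. It reproduces: 43 evaluable infants per group by the two-sample t test (power 0.801), 43 / 0.80 = 53.75, rounded up to 54, and 54 × 3 = 162. It has no bearing on this point.

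**Assumed inputs (none from the document).** A simulation of 400,000 infants used:
- lognormal time to recovery, median 72 h, SD 0.6 on the log scale;
- referral time uniform between 3 and 36 h, independent of recovery time;
- 0%, 5%, 10% or 20% of infants assigned to referral. The share q actually referred is slightly lower (0.048, 0.096 and 0.194 for the last three), because some infants recover first.

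**Three treatments of referral, median time to recovery:**

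| Assigned to referral | (a) Referral = end of stay | (b) Referral censored | (c) Referred = not recovered |
|---|---|---|---|
| 0% | 72 h | 72 h | 72 h |
| 5% | 69 h | 72 h | 75 h |
| 10% | 66 h | 72 h | 78 h |
| 20% | 59 h | 72 h | 86 h |

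**Hand check at 72 h.** Half of the infants would have recovered by then, and all referrals have occurred. The share counted as recovered is about q + (1 − q) × 0.50 under (a) and (1 − q) × 0.50 under (c).
- q = 0.096: (a) 0.096 + 0.904 × 0.50 = 0.548; (c) 0.452. Simulation: 0.549 and 0.452.
- q = 0.194: (a) 0.194 + 0.806 × 0.50 = 0.597; (c) 0.403. Simulation: 0.600 and 0.406.

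**Between arms.** Suppose one arm has 5% and another 10% assigned to referral, with recovery otherwise identical. In 54 infants that is 54 × 0.05 = 2.7 and 54 × 0.10 = 5.4.
- (a) 69 against 66 h: the arm with more referrals appears 3 h faster.
- (b) 72 against 72 h: no difference appears.
- (c) 75 against 78 h: the arm with more referrals is 3 h slower.

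Column (b) is flat by construction, since referral was made independent of recovery time. If referred infants would have recovered later than the rest, censoring them would also remove slow recoveries from the curve.

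**The case against.** **An unstated censoring rule for a secondary outcome is normally left to the analysis plan.** That would be right if only the rule were missing. Here the measure, the end of participation and the method are all stated, and together they leave no place for a referred infant as unrecovered. It does stand that the article does not say which of the two labels will be used. A reader might infer that referred infants will be scored as early recoveries, but the text does not settle that.

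**Time at hospital could include intensive care.** Read literally, Table 2 allows this, and a referred infant would then have a long stay. The reading is possible but unstated. It sits badly with participation ending at referral and with the abstract's reference to the ward.

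**Fisher's exact test.** A reader might infer that naming it is an error. The document does not support that: the test can properly compare the proportion recovered by a fixed time, alongside a Kaplan-Meier description. What stands is that no time point is named.

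**Harm is not hidden.** Referral is its own secondary outcome, and an independent statistician looks at safety at the interim analysis. A claim that deterioration is lost from the trial would go too far. Separate reporting does not, however, correct the recovery-time comparison.

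**Direction.** A reader might infer that the bias works against the interventions. That would require fewer referrals under treatment, which the document gives no basis to assume. With equal referral in all arms, this mechanism favours no arm.

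**Conclusion.** The point holds as an inconsistency between three stated elements: hospital or ward time as the measure, participation ending at referral as well as at discharge home, and Kaplan-Meier as the method. Under them a referred infant contributes either a short stay or a censoring time treated as non-informative. The arm with more referrals then looks better on this outcome than it is.

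The size cannot be known from the document. Under the assumed inputs the median moves down by 3 h at 5% referral, 6 h at 10% and 13 h at 20% if referral ends the stay. It does not move if referral is censored. It should move up by 3, 6 and 14 h if referred infants count as not recovered. These sizes depend on the assumed distribution and timing, and few referrals mean a small effect. Bias between arms arises only if referral differs by arm. This is worth correcting before analysis, but it concerns one secondary outcome and leaves the primary analysis and the sample size of 162 untouched.

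**What to change.** 1. Define the event as discharge home, timed from randomisation. Infants may be included up to 24 h after admission, so the origin should be explicit.
2. Treat intensive care referral as a competing event and report the cumulative incidence of discharge home by arm. Alternatively, within SPSS, keep referred infants at risk as not discharged to the end of observation and compare arms with a log-rank test.
3. Censor only at parental withdrawal.
4. In any rank test of hours, rank referred infants last.
5. If Fisher's exact test is kept, state that it compares the proportion discharged home by a prespecified hour, with referred infants counted as not discharged.
6. Align the wording of Table 2 and the abstract with this definition.

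**Cost.** A change of analysis text, with no added infants and no data needed after referral. The estimate becomes cumulative discharge home rather than mean hours. The time of referral must be taken from the end-of-participation record. Table 2 lists referral only as yes or no, so it should be confirmed that this time is captured.

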#### Primary outcome measures

A clinical index combining levels of oxygen saturation, oxygen concentration (need for oxygen supplementation), high nasal flow treatment, and oral fluid intake (compared to tube feeding) was constructed; see Table 1. It is possible to achieve a total score between 0 (worst condition) and 11. The primary outcome is a composite index that the research group constructed for this study, based on the factors that determine whether the infant needs hospitalisation [28]. The items in the index were chosen because of their clinical implication. They are based on objective values and are therefore not likely to differ between different assessors. The index has not been validated, but was tested in a small pilot study (unpublished material), where the clinically relevant change of two points was determined by clinical reasoning.

**Table 1 Tab1:** The components of the clinical index used as the primary outcome measure

Outcome	Definition	Measure	Registration time	Score
**Oxygen saturation**	%	By pulse oximetry	At t1, t2, and every subsequent 3rd hour	
	≥ 96			2
	90–95			1
	≤ 89			0
**Oxygen concentration**	%		At t1, t2, and every subsequent 3rd hour	
	21			4
	22–30			3
	31–40			2
	41–50			1
	≥ 51			0
**High nasal flow**	Litres/kg/min		At t1, t2, and every subsequent 3rd hour	
	0			2
	0.1–1			1
	1.1–2			0
**Oral fluid intake**	%^a^	g (weight when breast feeding) or ml (by bottle)	At every feeding session	
	100			3
	51–99			2
	1–50			1
	0			0

^a^Per cent of the calculated daily need

The daily fluid need will be calculated according to nutrition guidelines [29, 30]. The oral fluid intake for analysis at hour 24 will be the collected intake during the first 24 h in the study.

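### Infants discharged before hour 24 are excluded from the primary analysis by rule, and those referred to intensive care drop out by implication, so a real effect is pulled towards zero

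*Protocol article*

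**What the plan says.** All places are in the protocol article.

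- **Endpoint and model** (Statistical and sample size calculations): "The primary outcome is clinical index at 24 h", and the group effect "will be assessed by an ANCOVA model with adjustment for baseline clinical index".
- **Analysis set** (same section): "The primary analysis will include all participants with available outcome data at 24 h. Drop-outs will not be included in this analysis".
- **Early discharge** (same section): "If an infant will be discharged from the ward before hour 24, that participant will be excluded from this analysis". The sentence goes on to treat such an infant like any other drop-out.
- **Intensive care.** The statistics section has no rule for it. The section on inclusion of participants says: "The participation in the study will end when the infant is either discharged to the home or referred to an intensive care unit".
- **Imputation** (statistics section): "A dataset with the imputed values might also be analysed". It "will be performed if data is missing at hour 24 and the patient is still at hospital".
- **What the index measures** (Primary outcome measures): it is "based on the factors that determine whether the infant needs hospitalisation", scored from 0 (worst) to 11.
- **Related provisions.** The sample size allows for about 20% incomplete observations and drop-outs. Drop-outs are to be described by allocation group and severity at admission, among other factors. Time at hospital and intensive care referral are secondary outcomes, and recovery time has a Kaplan-Meier analysis.

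**The concern.** An infant who goes home before hour 24 has done about as well as the index allows, and one who goes to intensive care has done badly. Neither absence is missing data in the ordinary sense: both exits are outcomes on the construct that the endpoint measures. The infants left are those ill enough to stay but not ill enough to be transferred. If treatment changes who falls into that middle group, the groups compared at 24 h are no longer the randomised groups.

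The trial's own rationale makes this matter. The Discussion asks for treatments that lessen the need for hospital care, and the primary analysis removes the infants in whom that happens soonest. At stake is the primary estimate itself: a working intervention would look weaker than it is, and a harmful one less harmful.

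**Working it through.** **1. The plan's sample size reproduces.** Two-sided two-sample t test, difference 2, SD 2.8, alpha 0.016. Exact power is 0.801 at 43 per group and 0.790 at 42, so 43 is right. Then 43 / 0.80 = 53.75, rounded up to 54 per group, and 3 × 54 = 162. The arithmetic is sound, but the 20% allowance restores numbers, not comparability.

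**2. Which rule applies to which infant.**

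| Status at hour 24 | Primary analysis | Optional imputed dataset |
|---|---|---|
| In hospital, index recorded | included | included |
| In hospital, index missing | excluded | included |
| Discharged home earlier | excluded by stated rule | excluded |
| Referred to intensive care earlier | excluded by inference | unclear |

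The reference to this analysis in the discharge sentence could mean the primary or the imputed analysis. Discharged infants are in neither. A transferred infant may still be at hospital, so carrying a pre-transfer value forward in the optional dataset is not ruled out. That does not affect the primary analysis.

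**3. Early discharge need not be rare.** The article expects the majority to be inpatients still at that time but gives no figure. Enrolment may be up to 24 h after admission, so study hour 24 can fall up to 24 + 24 = 48 h after admission.

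**4. One case by hand.** Assume a normal index with SD 2.8, a true benefit of 2, and exit whenever 24 h status passes one threshold that 10% of controls exceed.

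- Control threshold: z = 1.282. In the treated arm: 1.282 − 2/2.8 = 0.567, so 28.5% exceed it.
- Mean of those retained = arm mean − 2.8 × φ(z)/Φ(z), with the control arm mean set to 0.
- Control: −2.8 × 0.1755/0.900 = −0.55. Treated: 2 − 2.8 × 0.3397/0.7147 = 0.67.
- Retained difference: 0.67 + 0.55 = 1.22 instead of 2, without baseline adjustment.

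**5. With the planned baseline adjustment.** Large-sample simulation of the ANCOVA. Assumptions: true difference 2, SD 2.8, correlation with baseline 0.5, unbounded index, and exit driven by 24 h status under the same rule in both arms, with added noise of 0 to 1 SD. The ranges run over the noise.

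| Assumed exit in control | Exit in treated arm | Estimate (true 2) |
|---|---|---|
| Discharge 5% | 13–18% | 1.5–1.8 |
| Discharge 10% | 22–29% | 1.35–1.7 |
| Discharge 20% | 37–45% | 1.1–1.6 |
| Intensive care 5% | 1–2% | 1.8–1.9 |
| Discharge 10% and intensive care 5% | 23–29% | 1.1–1.6 |

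With a true difference of 0, exits are balanced and the estimate is about 0 in every scenario.

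**6. On the bounded 0–11 scale** (no baseline adjustment, sharp thresholds). Control mean 7, discharge at a latent index of 11 or more (8% against 24%): the difference is 1.70 in all infants and about 1.3 in those retained. Control mean 6, discharge at 10 or more and intensive care at 1 or less: about 1.8 against 1.1. With a true shift of −2, the retained differences are about −1.65 and −1.19.

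**The case against.** **The size rests on invented inputs.** This stands. The article gives no mean index at 24 h and no rate of early discharge or transfer. Sharp thresholds give the largest bias; with noisy exit and 5% control discharge the loss may be only 0.2 points.

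**Part of any power loss is already paid for.** This also stands. In the first bounded-scale case, power is 0.89 with all 54 infants per arm and 0.64 with those retained, but the plan budgets for 43 evaluable infants, where full-data power is 0.80. The fair contrast is roughly 0.80 against 0.64.

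**The intensive care half is not stated.** Correct: it follows from reading two sections together and is weaker than the discharge half.

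**The plan makes differential exit visible.** The description of drop-outs, the two secondary outcomes and the Kaplan-Meier analysis would show it. They do not return these infants to the primary comparison.

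**Assigned scores are a convention.** True. An infant can go home below 11, which requires saturation of at least 96% and full oral intake, and intensive care need not mean 0. That is a reason for sensitivity analyses, not for exclusion.

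**Two stronger readings are tempting.** A reader might infer that a harmful treatment would look neutral. The calculations do not show this: a shift of −2 remains clearly negative. A reader might also infer that the interim harm check would miss infants sent to intensive care. The article does not restrict that check to the index, records referral as a yes/no outcome, and leaves further instructions to the trial team.

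**Conclusion.** The point holds. The primary analysis set depends on a post-randomisation outcome of the endpoint's own construct, explicitly for discharge and by inference for intensive care. The optional imputation never covers discharged infants.

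The bias is conditional. With no effect on any infant there is none, so the rule does not in itself create false positive results under this model. If treatment changes early exit, the estimate moves towards zero for benefit and harm alike, provided that exit depends on the infant's status in the same way in all arms. The size cannot be fixed from the article. Over 5–20% assumed control discharge, a true 2-point difference becomes about 1.1–1.8 after baseline adjustment. Exclusions also become unequal: 10% in control goes with 22–29% in an effective arm, and 8% with about 24% if exit is sharp. Both exceed the 20% allowance before any other missing data, including the extra exclusions from the physiotherapy arm that the Discussion expects.

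**What to change.** - **Primary analysis:** all randomised infants as allocated, with a pre-specified value or rank for each exit before hour 24. For example, discharge home takes the best score, 11, and intensive care referral the worst, 0. Keep the planned ANCOVA and support it with a rank-based analysis, because values will cluster at the ends of the scale.
- **Other missing 24 h values:** impute from the three-hourly data. State how oral intake is handled, since at hour 24 it is the total over the first 24 h in the study.
- **Sensitivity analyses:** the observed-case analysis as now planned, and one with less extreme assigned values.
- **Timing:** fix these rules before any results by arm are seen.

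The cost is analysis-plan wording. Time at hospital and intensive care referral are already recorded, and the last three-hourly assessment should date an exit. The small downside is that the assigned scores are conventions and may move the SD away from the pilot's 2.8. The planned interim check of the SD can verify this if it uses the same endpoint definition.
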